## Abstract

**Background:**

A temporary loop ileostomy, which is used to decrease the risk of symptomatic anastamotic leakage after anterior resection and total mesorectal excision (TME), is traditionally closed without any mesh. However, as 44% of incisional site hernias need further repair after stoma closure, attention has increasingly been paid to the use of mesh. Research on the prevention of these hernias is scarce, and no studies comparing different meshes exist.

**Method/Design:**

The Preloop trial (Clinical Trials NCT03445936) is a prospective, randomized, controlled, multicenter trial to compare synthetic mesh (Parietene Macro™, Medtronic, Minneapolis, MN, USA) and biological implants (Permacol™, Medtronic) at a retromuscular sublay position for the prevention of incisional site hernias after loop-ileostomy closure. The main endpoints in this trial are infections at 30-day follow-up and the incidence of hernias clinically or on CT scan at 10 months after closure of the stoma. The secondary endpoints are other complications within 30 days of surgery graded with the Clavien-Dindo classification, reoperation rate, operating time, length of stay, quality of life measured with RAND-36, and incidence of hernia over a 5-year follow-up period. A total of 100 patients will be randomized in a 1:1 ratio.

**Discussion:**

This is a pilot trial that will be undertaken to provide some novel evidence on the safety profile and efficiency of both synthetic mesh and biological implants for the prevention of incisional hernias after closure by temporary loop ileostomy. The hypothesis is that synthetic mesh is economical but equally safe and at least as effective as biological implants in hernia prevention and in contaminated surgical sites.

**Trial Registration:**

ClinicalTrials.gov, NCT03445936. Registered on 7 February 2018.

## Background and rationale

Anastomotic leakage is a major cause of morbidity after sphincter-saving anterior resection and total mesorectal excision (TME), with a reported incidence in a large meta-analysis of 11% [1]. A temporary diverting stoma has been shown to significantly decrease the risk of symptomatic anastomotic leakage and the need for reoperation in meta-analyses [2–5]. Defunctioning loop ileostomy is superior to loop colostomy in terms of a lower surgical complication rate and fewer parastomal and incisional hernias and surgical site infections [6, 7].

In a recently published retrospective study by Juratli et al., the incidence of incisional hernias after loop-ileostomy closure detected by computed tomography (CT) scan 12–24 months later reached 21.5% [8]. Another retrospective cohort showed an incisional hernia incidence of 13.5% after loop-ileostomy closure after a median follow-up of 20 months [9]. Of these clinically detected incisional hernias, 44% needed further surgical repair upon meta-analysis [10]. The true rate of incisional hernias might be higher, though, as the incidence of hernias increases over time [11, 12].

So far, the fear of infectious complications has discouraged the use of synthetic mesh in contaminated surgical fields. Nevertheless, the infection rate of patients with synthetic prophylactic mesh applied in contaminated surgical fields is similar to that of controls without the mesh at the time a permanent stoma was created [13–16]. The use of synthetic meshes as prophylaxis has also been shown to be safe in other contaminated abdominal surgery sites [15, 17].

There are only a few previous studies on prophylactic mesh utilization at the time of stoma closure. Biological mesh has been demonstrated to be safe in terms of complications [18, 19] and effective in preventing hernias [20]. However, no randomized controlled trials (RCTs) have been published. Reinforcement of Closure of Stoma Site (ROCSS) Collaborative and the West Midlands Research Collaborative has recently published a protocol for an RCT comparing a standard suture closure to mesh reinforcement with biological intra-abdominal mesh after stoma closure [21]. Research on synthetic meshes in the same context is even rarer. An Australian study group found a significant reduction in the rate of incisional hernias following mesh placement without increasing the rate of infection complications, despite the use of prosthetic material in the contaminated surgical site [22]. In a register study, the application of synthetic mesh was found to be both safe and effective in preventing incisional site hernias after stoma closure [23]. There have been no trials comparing biological implants and synthetic mesh on incisional hernia prophylaxis.

Macroporous monofilament polypropylene mesh (Parietene Macro™, Medtronic) has previously been shown to be safe in contaminated surgical sites according to satisfactory preliminary results of the PREVENT trial in parastomal hernia prophylaxis [24]. Likewise, there have been no trials on the use of porcine dermal collagen implants to prevent hernias, although they have been widely studied for ventral hernia repair [25].

The ideal location for the prophylactic mesh is still unclear. In a recent meta-analysis that included all types of postoperative ventral hernias, the sublay location of mesh was associated with the lowest rate of infection and recurrence [26]. Based on the results of a meta-analysis on parastomal hernia prevention, the sublay position of a non-absorbable prophylactic mesh is preferred [16].

### Objectives

The objective of the Preloop trial is to compare synthetic mesh (Parietene Macro™, Medtronic) and biological implants (Permacol™, Medtronic) for the prevention of incisional site hernias after temporary loop-ileostomy closure (see Table 1). Our hypothesis is that synthetic mesh is equally safe and effective as biological implants in incisional site hernia prophylaxis, and that they both can significantly reduce the rate of incisional hernias detected in previous studies. Its lower price also makes synthetic mesh a more lucrative option. By demonstrating that synthetic mesh is equal to biological implants in terms of safety and efficiency, this study might encourage investigators to design upcoming trials that use synthetic materials in contaminated fields. As previous studies are scarce, the Preloop trial was planned as a pilot study to provide preliminary results on the safety and efficiency of both devices used in the study.

**Table 1 Tab1:** Comparison of devices in Preloop trial

Comparison of devices	Parietene Macro	Permacol
Manufacturer	Medtronic	Medtronic
Mesh type	Synthetic	Biological implant
Material	Macroporous monofilament polypropylene mesh	porcine dermal collagen implant
Size	Trimmed to fit retromuscular space, original size before trimming 10 × 15 cm	length 10 cm, width 5 cm

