### Devices trialed

Parietene Macro™ (Medtronic) is a macroporous monofilament polypropylene synthetic mesh widely used in hernia repair. Permacol™ is an acellular porcine dermal collagen implant designed for hernia repair (see Table 1). The size of the biological implant selected for this study (Permacol™, Medtronic) reflected a compromise of price. As the price of an implant increases significantly the larger it is, the chosen 10 cm in length and 5 cm in width represents a realistic option for use in general practice, *if* it is shown to be both effective and safe. The significantly more affordable synthetic mesh (Parietene Macro™, Medtronic) has been trimmed to fit the retromuscular space in width, as would be done in general everyday practice.

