#### Participant timeline

Randomization started in February 2018 at Oulu University Hospital and will last for 2 years. The follow-up schedule is presented in Table 2. Short-term results and complications will be monitored at discharge and 1 month after the operation. CT scans to detect subclinical hernias besides clinical evaluation will be performed 10 months after stoma closure as part of the routine protocol of rectal adenocarcinoma follow-up.

**Table 2 Tab2:** Schedule of events

Schedule of events	Baseline	Procedure	Discharge	30 days ± 3 days	10 months ± 14 days	3 year ± 30 days	5 years± 30 days	Unscheduled visit
Informed consent	X							
Demographics and medical history	X							
QoL	X			X	X	X	X	
Procedure details		X						
CT scan findings					X			
Protocol deviation	X*	X*	X*	X*	X*	X*	X*	X*
Complications		X*	X*	X*	X*	X*	X*	X*
Study exit form							X**	

*Complete if applicable

**Complete when lost to follow-up, consent withdrawal, or when the subject has completed all study-related visits

*CT* computed tomography, *QoL* quality of life

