#### Sample size

Two of the previously published retrospective studies reported the incidence of incisional hernias to be 13.5–21.5% on short-term follow-up after closure by suturing [8, 9]. Likewise, the number of hernias after closure with mesh has been very few in short-term follow-up [20, 22]. We assume that the hernia rate after closure by suturing detected in previous studies can be significantly diminished to about 5% with a prophylactic synthetic mesh or biological implant on long-term follow-up. The aim of the study is to generate preliminary results showing synthetic mesh is non-inferior to biological mesh. Assuming α = 0.05 and a power = 80% for incisional hernias and with 5% non-inferiority marginal, we would need 235 patients per group. Although previous studies on both biological implants and synthetic meshes have raised no concerns on the safety of the meshes [18–20, 22, 23], the use of synthetic meshes in contaminated surgical sites continues to be widely avoided in clinical practice, and no comparative studies on incisional hernia prophylaxis after temporary stoma closure exist. That said, we assume there is no difference in infectious complications between the meshes.

As this is a pilot study, each group will comprise 45 patients. Considering a possible 10% drop-out rate, our aim is to have 50 patients per group. Therefore, the estimated sample size of 50 in each group should give a reliable preliminary estimation of the safety and efficiency of both meshes for further studies.

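### The hypothesis that both devices reduce hernias against past suture rates cannot be tested: there is no suture arm, and the 10-month endpoint is earlier than those rates

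*Protocol article*

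**What the plan says.** The protocol article states two hernia hypotheses under Objectives. The first is that synthetic mesh is as effective as the biological implant, which the randomisation addresses. The second is "that they both can significantly reduce the rate of incisional hernias detected in previous studies". Under Trial design and Closure of stoma site, both groups receive a device; no group is closed by suture alone.

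The earlier rates are dated in Background and rationale. One retrospective study gives hernias "detected by computed tomography (CT) scan 12–24 months later reached 21.5" per cent; another gives "an incisional hernia incidence of 13.5% after loop-ileostomy closure after a median follow-up of 20 months". The same paragraph says the true rate may be higher, "as the incidence of hernias increases over time". The Sample size section cites both studies as having "reported the incidence of incisional hernias to be 13.5–21.5% on short-term follow-up after closure by suturing", and places the assumed device rate of about 5% at long-term follow-up.

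The main hernia endpoint is clinical and/or radiological detection at 10 months (Outcomes, Statistical methods). Under Participant timeline, "CT scans to detect subclinical hernias besides clinical evaluation will be performed 10 months after stoma closure", and Table 2 marks CT at no other visit; the later visits are at 3 and 5 years.

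On the biological implant, the Background reports "no trials on the use of porcine dermal collagen implants to prevent hernias, although they have been widely studied for ventral hernia repair". Devices trialed adds: "The size of the biological implant selected for this study (Permacol™, Medtronic) reflected a compromise of price".

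Statistical methods gives a proportion with a 95% confidence interval for each group, χ² or Fisher tests between groups, and two-tailed p values.

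**The concern.** A claim that both devices reduce hernias needs a rate without a device, taken at the same time and by the same method. The trial has no such arm, and the past rates it names were taken later than its own endpoint. Since the protocol itself says incidence grows with time, a 10-month figure below 13.5% or 21.5% may partly or wholly reflect less follow-up.

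Similarity between the arms does not close the gap. It would imply prevention only if the reference device were known to prevent hernias in this setting. The protocol reports no prevention trials of that material and presents the chosen implant size as still to be shown effective.

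What is at stake is how the pilot is read. The Discussion says it should form the basis for future trials. A low rate in either arm, or two similar rates, could be carried forward as evidence of prevention that the design does not provide.

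**Working it through.** **1. The plan's own figure.** Sample size gives 235 per group for 5% versus 5%, margin 5 points, α = 0.05, power 80%. With one-sided α: n = (1.645 + 0.842)² × 2 × 0.05 × 0.95 / 0.05² = 234.9, so 235. The figure reproduces and is device versus device. The planned evaluable size is 45 per group.

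**2. Time points side by side.**

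| Quantity | Value | Time | Detection |
|---|---|---|---|
| Past suture rate | 21.5% | 12–24 months | CT |
| Past suture rate | 13.5% | median 20 months | not stated clearly |
| Assumed device rate | about 5% | long-term | not stated |
| Trial endpoint | – | 10 months | clinical and/or CT |

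**3. What one arm of 45 can show.** Exact (Clopper-Pearson) 95% upper limit for x hernias, the 0.975 quantile of Beta(x + 1, 45 − x):

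| x | 0 | 1 | 2 | 3 | 4 | 5 |
|---|---|---|---|---|---|---|
| Upper limit | 7.9% | 11.8% | 15.1% | 18.3% | 21.2% | 24.1% |

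The limit is below 13.5% for x ≤ 1 and below 21.5% for x ≤ 4. At a true 5%, P(2 ≤ X ≤ 4) = 0.927 − 0.335 = 0.592. So in 59% of cases an arm would look better than one past rate but not the other.

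**4. Possible effect of timing (illustrative).** The documents give no timing curve, so assume hernias arise at a constant rate. A rate r reached at T months becomes 1 − (1 − r)^(10/T) at 10 months. The next-to-last column is the chance that an arm of 45 that prevents nothing has an upper limit below the unadjusted past rate. The last column is the same chance if timing did not matter.

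| Past rate | T (months) | At 10 months | Chance, constant rate | Chance, no timing effect |
|---|---|---|---|---|
| 13.5% | 20 | 7.0% | 17% | 1.2% |
| 21.5% | 24 | 9.6% | 56% | 2.3% |
| 21.5% | 18 | 12.6% | 32% | 2.3% |
| 21.5% | 12 | 18.3% | 7% | 2.3% |

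These chances describe an informal reading of the interval, not a planned test. The 13.5% rows treat a median follow-up of 20 months as if everyone were observed for exactly that long, and they ignore any difference in detection.

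**5. What the randomised comparison can show.** Newcombe 95% interval for the difference in proportions, 45 per arm. For 2/45 the Wilson limits are 1.2% and 14.8%, so with 2 versus 2 the half-width is √[(4.4 − 1.2)² + (14.8 − 4.4)²] ≈ 10.9 points:

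- 2 versus 2: difference 0, 95% CI −10.9 to +10.9 points.
- 3 versus 2: difference +2.2, 95% CI −9.0 to +13.9 points.

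Fisher's two-tailed p is 1.0 in both cases. That p value says nothing about how large a difference remains possible; the interval does.

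**The case against.** The strongest reply is that the protocol never plans the faulted comparison. The reduction clause names no time point, and Statistical methods contains no test against a historical rate. The probabilities in step 4 are thus error rates of a rule the protocol does not contain. This stands, and it is why the point is limited to the wording of the hypothesis and to informal reading.

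Second, the 5% is placed at long-term follow-up and hernia at 3 and 5 years is a secondary outcome. Against that horizon, longer follow-up would work against the devices. This is fair, but no CT is scheduled at those visits, neither matches 12–24 months, and there would still be no suture arm.

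Third, detection may offset timing. The sentence after the 13.5% speaks of clinically detected hernias. Its reference is unclear because it cites a meta-analysis, but if the 13.5% was clinical only, the trial's more sensitive endpoint would count against the devices. The direction of bias for that rate is therefore uncertain. The 21.5% was obtained by CT, so this does not apply to it in the same way.

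Fourth, the protocol calls biological mesh effective as a class, openly discloses the size compromise, and repeatedly labels the trial a preliminary pilot with a device-versus-device aim. All true. A declared pilot may still state a hypothesis its design cannot address.

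A reader might infer that the trial plans a biased historical test, or that a useless device would be declared effective in up to 56% of trials. The documents support neither: there is no such test, and that figure depends on a constant rate and on placing the 21.5% at 24 months.

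**Conclusion.** The point holds as a minor fault. The design cannot support the hypothesis that both devices reduce the hernia rate of previous studies, because there is no suture arm and the main endpoint precedes both past rates. That conclusion rests on the protocol's text alone. The size of the timing effect does not: under a constant rate the past suture rates correspond to roughly 7–18% at 10 months, but this is illustration. For the 21.5% the timing favours the devices; for the 13.5% the net direction is unknown.

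The randomised comparison, sample size and data collection are untouched. That comparison is the hernia conclusion the trial can deliver, and at 45 per group it is imprecise, with an interval of about ±11 points when each arm has 2 hernias. Separate intervals for each arm and two-tailed p values do not express it well, since a non-significant p value is not evidence that the devices are equally effective.

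**What to change.** 1. In Objectives and Statistical methods, define the hernia conclusion as the difference in 10-month hernia proportion, synthetic minus biological, with its 95% confidence interval (for example Newcombe), instead of relying on two-tailed χ² or Fisher p values.

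2. Replace the reduction clause in Objectives with a statement that the trial does not test whether either device prevents hernias compared with suture closure. Where past rates are shown beside the results, present both 13.5% and 21.5% descriptively, without a pass/fail rule, and give their timing and detection method (CT at 12–24 months; median 20 months with the method as reported by the source) next to the trial's clinical and/or CT detection at 10 months.

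The cost is two or three sentences, with no extra patients, visits or data. The downside is that the pilot gives up a claim of reduction relative to suture.

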### Trial design

The Preloop trial (see also Fig. 1) is a prospective, randomized, controlled, multicenter study comparing two devices (synthetic mesh, Parietene Macro™, Medtronic; and biological implant, Permacol™, Medtronic) in preventing ileostomy site hernias, including in patients who have undergone low anterior resection and TME for rectal adenocarcinoma with diverting loop ileostomy. The trial is independent from any kind of industrial sponsorship.

**Fig. 1 Fig1:**
[figure not shown]
Flowchart

### Devices trialed

Parietene Macro™ (Medtronic) is a macroporous monofilament polypropylene synthetic mesh widely used in hernia repair. Permacol™ is an acellular porcine dermal collagen implant designed for hernia repair (see Table 1). The size of the biological implant selected for this study (Permacol™, Medtronic) reflected a compromise of price. As the price of an implant increases significantly the larger it is, the chosen 10 cm in length and 5 cm in width represents a realistic option for use in general practice, *if* it is shown to be both effective and safe. The significantly more affordable synthetic mesh (Parietene Macro™, Medtronic) has been trimmed to fit the retromuscular space in width, as would be done in general everyday practice.

## Methods

### Study setting

This study will be completed in several university and central hospitals in Finland: Oulu University Hospital, Turku University Hospital, Tampere University Hospital, Kuopio University Hospital, Jyväskylä Central Hospital, and Seinäjoki Central Hospital.

### Eligibility criteria

#### Inclusion criteria

Anterior resection and TME with temporary loop ileostomy for rectal adenocarcinoma without any adjuvant oncological treatmentAge 18 years or olderLife expectancy of at least 12 monthsSigned informed consent with agreement to attend all study visitsLoop-ileostomy closure within 2–4 months after the primary operation

#### Exclusion criteria

Presence of a comorbid illness or condition that would preclude surgical treatment (American Society of Anesthesiologists [ASA] grade 4–5).Concurrent or previous malignant tumors within 5 years before study enrollmentPresence of T4b tumors necessitating a multi-organ resectionPatients treated with postoperative adjuvant chemotherapyPatients undergoing emergency proceduresPrimary rectal surgery along with major concomitant procedures (e.g. hepatectomies, other intestinal resections).Metastatic disease with life expectancy of less than 12 monthsPregnancy or suspected pregnancy

All subjects who have had anterior resection and TME for rectal adenocarcinoma at any of the study sites and have not received any adjuvant oncological treatment due to routine protocol of rectal cancer treatment will be considered for inclusion at 1-month follow-up at the outpatient department after the primary operation. The current practice at Oulu University Hospital is to close temporary loop ileostomy by suturing the fascial defect without a mesh at either 2–4 months after uncomplicated anterior resection or about 8–12 months after anterior resection after adjuvant oncological treatment has been accomplished. A full-body CT scan is part of the 1-year follow-up protocol after anterior resection for rectal adenocarcinoma. Therefore, only subjects not receiving adjuvant treatment can be enrolled in the study without having any additional radiation and still undergo a CT scan for both cancer follow-up and detection of possible incisional hernias about 1 year from each operation. After receiving proper information on the possible advantages and disadvantages of intervention, and after voluntarily signing the informed consent form, the subjects will be enrolled in the Preloop trial.

Participating investigators are qualified colorectal or general surgeons experienced in the surgical management of patients with temporary stomas. Further, all participating surgeons are experienced in the relevant technique for loop-ileostomy closure procedures and the use of retromuscular meshes. The technique that will be used to apply both the synthetic mesh and the biological implant is identical. Surgeon contributions to the study will be limited to no less than 10 cases per hospital, and all attending hospitals will be directed to assign the operations to specific surgeons to eliminate potential sources of bias.

### Interventions

#### Primary procedure

Loop ileostomy will be established at anterior resection on a site previously marked by a trained ostomy nurse. The bowel forming the stoma will be everted about 1–2 cm above the skin and attached by Monocryl 4–0 sutures to the edges of the skin.

#### Closure of stoma site

The closure of the temporary loop ileostomy will be performed 2–4 months after uncomplicated anterior resection on subjects who had since received no adjuvant treatment. The re-establishment of intestinal continuity will be achieved through the ostomy trephine either by staples or by hand-sewn anastomosis, according to the surgeon’s preference, and the bowel will be positioned back into the peritoneal cavity. Midline laparotomy will be used in the case of extensive bowel adhesions. The posterior rectus sheath will be closed with interrupted 2.0 polydioxanone sutures (PDS Plus Antibacterial Suture, Ethicon, Johnson & Johnson, Somerville, NJ, USA). The retromuscular space will be dissected with monopolar diathermy or another suitable energy device to create the space for the mesh. In the first group, a biological implant measuring 10 cm in length and 5 cm in width with the corners slightly curved (Permacol™, Medtronic) will be placed in the retromuscular space established as described above. In the second group, a lightweight polypropylene mesh (Parietene Macro™, Medtronic) with measures matching the retromuscular space will be placed similarly into the retromuscular sublay position. Four interrupted 2.0 polydioxanone sutures (PDS Plus Antibacterial Suture, Ethicon, Johnson & Johnson), one in each corner of the mesh, will be used to fix the mesh to the underlying posterior rectus sheath. After mesh fixation, the anterior rectus sheath will be closed with interrupted 0 polydioxanone sutures (PDS Plus Antibacterial Suture, Ethicon, Johnson & Johnson). The skin defect will be closed by a running subcutaneous purse-string suture with a 2.0 polyglactin thread (Coated Vicryl Plus Antibacterial Polyglactin 910 Suture, Ethicon, Johnson & Johnson).

As a preoperative antibiotic, prophylaxis cefuroxime 1.5 g and metronidazole 500 mg administered intravenously (i.v.) will be used. Patients with a body mass index (BMI) ≥ 30 will receive cefuroxime 3 g and metronidazole 1 g i.v. If the patient has had a previous allergic reaction to primary prophylactic antibiotics, clindamysin 600 mg i.v. (or, in case of BMI ≥ 30, clindamysin 900 mg i.v.) and ciprofloxacin 400 mg i.v. will be administered. No mechanical bowel preparation will be given.

